#### Exploratory efficacy analyses

The following endpoints will be analysed in various exploratory analyses:

- Disease Control of Subsequent Second Line Treatments

Disease control rate defined as the ratio of the number of patients who had confirmed response (PR or CR) or stable disease (SD) according to the RECIST 1.1 criteria to the number of patients in analysis population (FAS, Per-protocol set, resp.). The disease control rates after the end of subsequent second line treatments will be compared between Vx-001 treated and placebo treated patients via two-sided Pearson’s chi-squared test (Statistical Table 25).

- Vaccine Specific Immune Response

Vaccine specific immune response (determined by the percentage of ARG-Vx001 specific T cells producing IFN-γ and/or perforin) will be evaluated by IFN-γ ELISpot® assay and perforin ELISpot® assay performed at baseline, after the second and sixth injection or end of treatment in case of the patient withdrawal from the study before or at Week 18 and from week 39, every 24 weeks.

The impact of the vaccine induced immune response on overall survival will be studied as follows:

Comparison of overall survival in patients with vaccine induced immune response detected after the second and sixth injection of Vx-001 (Statistical Table 26, Statistical Table 27, Figure 7, and Figure 8):

- - patients who received at least two and six injections of placebo, respectively,
  - patients randomised to Vx-001 who did not develop vaccine specific immune response after the second and sixth injections of Vx-001, respectively.

Comparison of overall survival in Vx-001-treated vs placebo-treated patients who had (Statistical Table 28, Statistical Table 29, Figure 9, Figure 10):

- a vaccine specific immune response before Vx-001 or placebo injection,
- high level of TERT expression or low level of TERT expression in their tumour biopsy.

These comparisons will be done using Kaplan Meier survival curves and two-sided Logrank test on FAS set.

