#### Other Exploratory Analyses

More general variants of Cox proportional hazards models will be applied to evaluate the influence of different prognostic factors, stratification factors, baseline characteristics on the treatment effect to time-to-death. Two-sided 95% confidence intervals of the hazard ratios of the treatment effect will be provided for each analysis on FAS set (Statistical Table 30, Figure 11). Additionally to stratification factors (Response to first line chemotherapy: objective response vs. stable disease, Squamous vs. non-squamous, Stage IV vs. recurrent stage I-III) and prognostic factors (Level of tumor TERT expression: low vs. high, Vaccine specific immune response status: naturally occurring response vs. absence of naturally occurring response) the following baseline characteristics will be included:

- - Age (at informed consent signing) : <65 and ≥65 years,
  - gender,
  - ECOG Performance Status,
  - smoking history,
  - First line chemotherapy (see section 8 for details on the grouping used).

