## Statistical/Analytical issues

### Adjustments for Covariates

All Cox models for all time-to-event endpoints, including for sensitivity analysis of the primary endpoint will be adjusted for the following stratification factors and prognostic factors:

- stratification factors:
  - Response to first line chemotherapy: objective response vs. stable disease,
  - Squamous vs. non-squamous,
  - Stage IV vs. recurrent stage I-III,
- prognostic factors:
  - Level of tumor TERT expression: low vs. high,
  - Vaccine specific immune response status: naturally occurring response vs. absence of naturally occurring response.

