### Examination of Subgroups

No specific subgroup analysis will be done but descriptive statistics will be presented on each stratification factors subgroups for the primary endpoint *i.e*.:

- - Response to first line chemotherapy: objective response
  - Response to first line chemotherapy: stable disease,
  - Squamous
  - non-squamous,
  - Stage IV
  - recurrent stage I-III,

The same descriptive analyses will be performed for each prognostic factors subgroups i.e.:

- - Level of tumor TERT expression: low
  - Level of tumor TERT expression high,
  - Vaccine specific immune response status: naturally occurring response
  - Vaccine specific immune response status: absence of naturally occurring response.

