| **Primary Objective:**  The primary objective is to compare survival rate at 12 months in Vx-001 treated vs placebo treated patients  **Secondary Objectives:**  Time-to-event comparison of overall survival in Vx-001 treated vs placebo treated patients.  **Exploratory Objectives:**  Comparison of survival rate at 12 months in patients with vaccine induced immune response detected after the second and sixth injection of Vx-001 *vs*  •patients who received at least two and six injections of placebo, respectively,  •patients randomised to Vx-001 who did not develop vaccine specific immune response after the second and sixth injections of Vx-001, respectively.  Comparison of survival rate at 12 months in Vx-001-treated *vs* placebo-treated patients who had:  •a vaccine specific immune response before Vx-001 or placebo injection,  •high levels of TERT expression or low levels of TERT expression in their tumour biopsy. | **Primary Objective:**  The primary objective is a time-to-event comparison of overall survival in Vx-001 treated vs placebo treated patients  **Secondary Objectives:**  Comparison of survival rate at 12 months in Vx-001 treated vs placebo treated patients.  **Exploratory Objectives:**  Comparison of overall survival in patients with vaccine induced immune response detected after the second and sixth injection of Vx-001 *vs*  •patients who received at least two and six injections of placebo, respectively,  •patients randomised to Vx-001 who did not develop vaccine specific immune response after the second and sixth injections of Vx-001, respectively.  Comparison of overall survival in Vx-001-treated vs placebo-treated patients who had:  •a vaccine specific immune response before Vx-001 or placebo injection,  •high levels of TERT expression or low levels of TERT expression in their tumour biopsy. |

The objective of the other exploratory analyses (5.2.4.5) is to evaluate the influence of different prognostic factors, stratification factors, baseline characteristics (age, gender, ECOG and smoking history) on the treatment effect to time-to-death using Cox proportional hazards models. The first line treatment at baseline is added to the list of factors explored in the Cox model because some of these first line therapies may have different impacts on the inflammatory and/or immune responses to the tested vaccine and hence influence the response to the vaccine.

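### The exploratory Cox models are meant to show what influences the vaccine effect, but no treatment-by-factor interaction is specified, so the models as described cannot estimate a difference in effect

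*SAP*

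**What the plan says.** Two sections state an aim of effect modification. SAP 5.2.4.5 (Other Exploratory Analyses) applies Cox models "to evaluate the influence of different prognostic factors, stratification factors, baseline characteristics on the treatment effect to time-to-death". Section 6 repeats that aim and adds first-line treatment because "some of these first line therapies may have different impacts on the inflammatory and/or immune responses to the tested vaccine" and so could alter how patients respond to the vaccine.

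The analysis is described as adjustment. In 5.2.4.5 the factors are to be included, and the output is given as: "Two-sided 95% confidence intervals of the hazard ratios of the treatment effect will be provided for each analysis on FAS set". Section 5.3.1 (Adjustments for Covariates) begins "All Cox models for all time-to-event endpoints, including for sensitivity analysis of the primary endpoint will be adjusted for the following" and lists the stratification and prognostic factors. Figure 11 in Appendix 2 is titled as overall survival adjusted for the factors.

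Section 5.2.4.4 separately compares Vx-001 with placebo in patients who had "a vaccine specific immune response before Vx-001 or placebo injection" and in those with "high level of TERT expression or low level of TERT expression in their tumour biopsy". The method is stated once for all of these: "These comparisons will be done using Kaplan Meier survival curves and two-sided Logrank test on FAS set".

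Section 5.3.8 (Examination of Subgroups) then says "No specific subgroup analysis will be done but descriptive statistics will be presented on each stratification factors subgroups", and gives the TERT and baseline-immunity subgroups the same descriptive treatment.

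**The concern.** Whether a factor influences the treatment effect is a question about a difference between hazard ratios. A Cox model with treatment and covariates as main effects gives one treatment HR, assumed equal at every level of every covariate. Adjustment can move that HR, but it cannot show that the HR differs between, say, high and low TERT expression. Followed as written, 5.2.4.5 leaves its own question unanswered.

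That leaves the separate log-rank results as the nearest available evidence for TERT. A reader who sees one level significant and the other not may conclude that TERT level predicts benefit, although two separate p-values do not measure a difference. At stake is a biomarker hypothesis carried into later development, not the primary conclusion of this trial.

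**Working it through.** **Inputs from the SAP.** Revised sample-size calculation: 12-month survival 43% (placebo) and 58% (vaccine), exponential; 200 evaluable patients, 1:1; one-sided 0.05; power about 82.5%; accrual 39 months; analysis when all patients have 6 months of follow-up. Exploratory tests are two-sided 0.05 (5.1.2). **Assumption:** the SAP gives no TERT split, so 50:50, 33:67 and 20:80 are used.

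**1. Reproduce the stated power.**
- Monthly hazards: −ln(0.43)/12 = 0.0703 and −ln(0.58)/12 = 0.0454, so HR = 0.645 and |ln HR| = 0.438.
- Probability of death by the analysis, with uniform accrual over A = 39 and F = 6 further months: 1 − [exp(−λF) − exp(−λ(A+F))]/(λA). This is 0.776 for placebo and 0.643 for vaccine.
- Deaths: 100 × (0.776 + 0.643) ≈ 142.
- Power, one-sided 0.05: 83.2% (Schoenfeld) and 82.2% (Freedman). The stated 82.5% is reproduced and is not in dispute.

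**2. Separate TERT tests when the true HR is 0.645 in everyone.** Power in a subgroup with d deaths is Φ(√(d/4) × 0.438 − 1.96). The subgroups contain different patients, so P(exactly one significant) = p1(1 − p2) + p2(1 − p1).

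| Assumed split | Deaths | Power in each | Exactly one significant |
| --- | --- | --- | --- |
| 50:50 | 71 / 71 | 45% / 45% | 50% |
| 33:67 | 47 / 95 | 32% / 57% | 53% |
| 20:80 | 28 / 114 | 21% / 65% | 58% |

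These tests run on the FAS, which the SAP assumes to be all 220 randomised patients. That gives about 156 deaths, or 78 per half: 49% power in each and again a 50% chance of a split result. If the vaccine has no effect in either level, the chance is 2 × 0.05 × 0.95 = 9.5%.

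**3. What an interaction test could show.** The SE of the log ratio of HRs is √(4/d1 + 4/d2). At 50:50 this is √(4/71 + 4/71) = 0.336. Power for a ratio of 0.645 (full design effect in one level, none in the other) is Φ(0.438/0.336 − 1.96) = 26%. It is 23% at 33:67 and 18% at 20:80. The ratio detectable with 80% power is 0.39, 0.37 and 0.31 respectively.

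**4. First-line regimen.** Section 8 lists nine categories. Spread evenly, 142/9 ≈ 16 deaths fall in each, too few for a useful HR per category.

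**5. Sections side by side.** Section 5.3.8 rules out specific subgroup analysis and limits TERT and baseline-immunity subgroups to description. Section 5.2.4.4 plans log-rank tests in the TERT subgroups and in patients with a baseline response. These cannot both stand as worded.

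**The case against.** The strongest reply is that 5.2.4.4 does what its objective asks. The exploratory objectives call for a comparison of survival between arms within the named subgroups, and a log-rank test answers that. This stands: a reader might infer that the log-rank tests are the wrong method, but they fall short only if used as evidence that the effect differs, which is the aim stated for the Cox models.

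A reader might also extend the 50% figure to all the factors. The document does not support that. Baseline immunity is log-rank tested only in patients with a prior response, so no pair of p-values arises, and regimen has no log-rank test. The figure applies to TERT alone.

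Next, 5.2.4.5 speaks of more general variants of Cox models and of hazard ratios in the plural, which does not exclude interaction terms. That is fair: the SAP does not forbid them. But none is named, and 5.3.1 and the Figure 11 title describe adjustment only.

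Finally, 5.1.2 and 5.3.5 declare all these tests illustrative and bar them from rescuing the study. This limits the consequences, but it does not make a main-effects model able to estimate a difference in effect.

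**Conclusion.** The point holds for the exploratory analyses. The SAP states an effect-modification aim in 5.2.4.5 and section 6 but describes only covariate adjustment, and no interaction or heterogeneity analysis is named. For TERT, the separate tests would give a split result about half the time under a uniform HR of 0.645 (50% to 58% over the assumed splits). This rests on the full design effect being true, since the figure is 9.5% with no effect, and on splits the SAP does not give. It should not be read as saying that a false biomarker claim is the expected outcome of the trial. The conflict between 5.3.8 and 5.2.4.4 is a matter of plain text and needs no assumption.

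**What to change.** - In 5.2.4.5, specify Cox models with a treatment-by-factor interaction, one factor at a time. Report the treatment HR in every level, including patients without a baseline immune response, and the ratio of HRs with its 95% CI.
- Group the nine first-line regimens into fewer categories and fix the grouping before unblinding. Section 6 does not say which component of the regimen matters, so the grouping should follow the sponsor's immunological rationale.
- State that any TERT difference is judged on the interaction estimate. The separate log-rank p-values may stay as illustrative results, since they serve a listed objective.
- Reword 5.3.8 so that it agrees with 5.2.4.4.

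The cost is SAP wording and a few model statements, with no new data. The drawback is low interaction power (about 18% to 26% for a ratio of 0.645). The SAP should therefore say that these results remain exploratory and that a non-significant interaction must not be read as a uniform effect.

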#### Other Exploratory Analyses

More general variants of Cox proportional hazards models will be applied to evaluate the influence of different prognostic factors, stratification factors, baseline characteristics on the treatment effect to time-to-death. Two-sided 95% confidence intervals of the hazard ratios of the treatment effect will be provided for each analysis on FAS set (Statistical Table 30, Figure 11). Additionally to stratification factors (Response to first line chemotherapy: objective response vs. stable disease, Squamous vs. non-squamous, Stage IV vs. recurrent stage I-III) and prognostic factors (Level of tumor TERT expression: low vs. high, Vaccine specific immune response status: naturally occurring response vs. absence of naturally occurring response) the following baseline characteristics will be included:

- - Age (at informed consent signing) : <65 and ≥65 years,
  - gender,
  - ECOG Performance Status,
  - smoking history,
  - First line chemotherapy (see section 8 for details on the grouping used).

### Safety analyses

Safety analysis will be based on the incidence, intensity, and type of adverse events, on clinical laboratory evaluations, physical exams, vital signs, ECG, ECOG performance status and local site reactions. Safety variables will be tabulated and presented for all subjects included in the Safety population (SAF).

#### Adverse events

**Adverse event listings:**

AE listings will be presented and sorted by subject, start date (calendar date and day from first vaccination administration), primary system organ class, preferred term and verbatim text for all adverse events recorded during the study and will include time since last vaccination and duration.

The following listings will be produced:

Listing of Adverse Events: (Listing 16.2.7.1) All adverse events for each patient, including the same event on several occasions, giving both preferred term and the original term used by the investigator. The listing will be sorted by site and by treatment group and should include: Patient identifier / Age, sex, weight, height / The adverse event (preferred term, reported term) / Duration of the adverse event / Severity according to NCI CTCAE / Seriousness (serious, non-serious) / Action taken with study treatment (none, permanent discontinuation, temporary discontinuation), / medication introduced / Outcome (resolved, resolved with sequelae, ongoing, lost-to-follow-up, fatal) / Causality relation to investigational treatment drug (not related, possible probable, definite) / Date of onset of the adverse event / Timing of onset of the adverse event.

Listings of Serious Adverse events, Adverse events leading to treatment discontinuation, Deaths, (Listing 16.2.7.2, Listing 16.2.7.3 and Listing 16.2.7.4 respectively), containing the same information as above

**Adverse events tabulations:**

Tabulation of adverse events will present for each cell the following information: number of patients with at least one occurrence of the event, corresponding percentage and number of events (if relevant). The following tables will be produced for all subjects included in the SAF population as well as by treatment group:

Summary table of adverse events (Statistical Table 32):

- Any AE
- Any TEAE
- Any drug-related TEAE
- Any TEAE leading to study drug discontinuation
- Any SAE
- Any treatment emergent SAE

For each category of the summary table of AE, 95% confidence intervals will be calculated for the incidence rates in each treatment group, together with a confidence interval for the treatment group difference in incidence rates.

A descriptive analysis will be performed for TEAEs. Global frequencies of SOC and PT will be calculated for:

- All TEAE by SOC an PT (Statistical Table 33)
- All not related TEAEs (*i.e.,* causality relationship to study drug is Not related) by SOC and PT (Statistical Table 34)
- All related TEAEs (*i.e.,* causality relationship to study drug is Possible, Probable or Definite) by SOC and PT (Statistical Table 35)
- All TEAEs by SOC and PT and by severity grade (Statistical Table 36)

Multiple counts within a PT or SOC (repeated or different included terms or changes in descriptors) will be considered only once per subject for the calculation of frequencies.

Depending on the number of TESAEs, similar tables as described above for TEAEs may be produced for TESAEs (Statistical Table 37, Statistical Table 38, Statistical Table 39 and Statistical Table 40). If the number of TESAEs is small, no specific tabulation of TESAEs will be produced.

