### Safety objectives

The safety objective is to compare the safety and tolerability of Vx-001 treated *vs* placebo treated patients.

The following parameters of safety and tolerability are assessed:

- Physical examination and vital signs
- Electrocardiogram
- Adverse event evaluation
- ECOG performance status (see Appendix 5: 10.5)
- Clinical laboratory evaluation: hematology and clinical chemistry

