The maximum duration of the treatment period for any patient for this study (comprising of the entire period of vaccinations until progression or withdrawal for any other reason) will be no more than the duration of the study. The duration of active follow up for survival and disease recurrence related to study participation will be dictated by the completion of the final analysis. Upon completion of the final analysis and if appropriate, patients under active treatment will continue to receive Vx-001 (the ARG-Vx001 peptide) within the remit of the study, until disease progression or marketing authorization of the vaccine and at the latest until the end of 2018. During this period patients will be followed-up every 12 weeks as described in the protocol. Patients under placebo treatment will stop to receive placebo and must undergo a complete final study termination visit and enter in the follow-up period for collection of survival data.

Treatment administration and duration:

- Investigational product:

Patients receive two vaccinations with 2mg TYR-Vx001 (weeks 0, 3), four vaccinations with 2mg ARG-Vx001 (weeks 6, 9, 12, 15) followed by vaccinations with 2mg ARG-Vx001 every 12 weeks commencing at week 27 until disease progression. If appropriate, patients, that have not progressed, will continue to receive Vx-001, until disease progression, unacceptable adverse events, death, major protocol violation, withdrawal of consent, or other reason as study closure.

Solutions for injection of Vx-001 peptides will be emulsified with adjuvant Montanide ISA51™ just prior to injection and will be administered subcutaneously.

- Reference therapy: Placebo:

Patients receive two subcutaneous injections with TYR-Vx001 Placebo at weeks 0, 3, followed by four vaccinations with ARG-Vx001 Placebo (weeks 6, 9, 12, 15) followed by injections of ARG-Vx001 Placebo at 12-week intervals commencing at week 27 until disease progression, unacceptable adverse events, death, major protocol violation, withdrawal of consent, or other reason as study closure, or study unblinding, if earlier.

Placebo solutions for injection will be emulsified with Montanide ISA51™ and will be administered subcutaneously.

The vaccination schedule is detailed in Figure 1.

Figure 1: Detailed schedule of vaccinations

Randomization:

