### Study assessments and study plan

One written Informed Consent Form (ICF) with two agreements (one to take part to the screening procedures and one to take part to the study) must be obtained. The first agreement documents the agreement to participate to the screening procedures, it should be obtained prior to initiating any screening specific assessments. The second agreement can be obtained at the screening procedure and at the latest at baseline visit and before the randomization. This second agreement documents the agreement to participate to the study. Only patients HLA-A*0201 positive with TERT expressing tumor and who have documented disease control can be randomized.

All baseline evaluations must be completed prior to initiating treatment with study medication.

Medical and physical examinations should be performed by a qualified physician and should include a thorough review of all body systems. Relevant data will be captured in the electronic Case Report Form (eCRF). All data will be recorded in source documents.

The study consists of the following phases/visits:

- Screening evaluation phase (HLA-A*0201 typing is necessary prior to any further screening, followed by assessment of TERT positivity of the tumor - access to tumor tissue biopsy is a pre-requisite. HLA-A2 patients with TERT expressing tumors will perform a CT scan / MRI to document disease control)
- Baseline visit, randomization and treatment allocation (Day 1 of week 0)
- Treatment period (visits every 3 weeks from randomization to week 15 and every 12 weeks from week 27 until the end of study treatment)
- Treatment assessment at week 18
- End of treatment (final) visit
- Survival follow-up contacts after the end of vaccination treatment (every 12 weeks, can be done by phone).

Patients have to visit the clinic/institution for investigational product administration and assessments according to the Flow Chart and Schedule of Assessments (see below).

|  | **Procedures** | **Screening period *** | **Baseline***** | **Treatment Period**  **Vaccination every 3 weeks** | | | | | **Treatment Evaluation** | **Treatment period**  **Vaccination every 12 weeks** | | **End of treatment (EOT)** | **Post Treatment Follow-Up Every 12 weeks** |
| --- | --- | --- | --- | --- | --- | --- | --- | --- | --- | --- | --- | --- | --- |

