### Adverse events

Any untoward medical occurrence in a patient or clinical investigation patient administered a pharmaceutical product and which does not necessarily have to have a causal relationship with this treatment.

An Adverse event (AE) can therefore be any unfavorable and unintended sign (including an abnormal laboratory finding), symptom, or disease (new or exacerbated) temporally associated with the use of a medicinal product, whether or not considered related to the medicinal product. The events occurring during pre-and post-treatment periods will also be designated as AEs. Therefore, reporting of such events, AEs and SAEs, will commence when the patient is enrolled into the study (date of signature of the informed consent) up until 4 weeks after the end of the treatment visits.

Adverse events (AE) will be coded using the latest available version of the Medical Dictionary for Regulatory Activities (MedDRA) and will be classified by MedDRA Preferred Term (PT) and System Organ Class (SOC).

Treatment Emergent Adverse Events (TEAE) will be defined as any adverse event that occur or worsen after the start of the study treatment *i.e.:*

- An AE that was not present prior to receiving the beginning of study treatment, or
- An AE that was present prior to receiving beginning of study treatment but which made the condition worse after the study treatment started.

Serious adverse events (SAE) are those AE that put the life of the patient at risk or that cause serious or permanent damage to the patient's health. An AE is to be recorded and reported as SAE in the event of any of the following:

- AE results in death
- AE is life-threatening
- AE requires hospitalisation or prolongation of existing hospitalisation
- AE results in persistent or significant disability or incapacity
- AE is a congenital anomaly or birth defect.
- AE is another medically important condition: This refers to an AE that may not be immediately life-threatening or results in death or hospitalization but may jeopardize the patient or may require intervention to prevent one of the outcomes listed above. Based on medical and scientific judgment (according to the investigator and or the sponsor) this should usually be considered serious.

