### Presentation of results

The following statistics will be presented:

- For quantitative variables: number of available data, number of missing values, mean, standard deviation, median, Q1, Q3, minimum and maximum values. When relevant, confidence intervals will be calculated for the mean (Student CI) or the median (Hahn &  [Meeker](https://scholar.google.fr/citations?user=vB55GXIAAAAJ&hl=fr&oi=sra) 1991).
- For qualitative variables: number of available data, number of missing values, number and percentage of observations in each category of the variable. Except if otherwise specified, percentages will be calculated using the number of available data as denominator (i.e., not including missing values). When relevant, confidence intervals of proportions will be calculated using the Clopper-Pearson method (Clopper & Pearson 1934).

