### Extent of exposure and compliance

Compliance with study treatment will be computed for each subject of the FAS and the PP populations as the proportion of vaccinations actually performed (see section 8). Treatment compliance will then be analysed globally and by treatment group, as a numerical variable as well as a categorical variable (see section 8, Statistical Table 18).

To analyse the extent of exposure the following variables will be summarised by treatment group for the SAF population (Statistical Table 31):

- number of vaccinations performed
- duration (number of days) between first IP administration and last IP administration.

The number of patients administered investigational product will be summarized according to the duration of treatment, separately for each treatment groups and in total. The compliance and the duration of treatment will also listed in Listing 16.2.5.1 and Listing 16.2.5.2, respectively

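### Table 32 compares the arms only on crude percentages of patients with an adverse event, although the observation window depends on time on treatment; a time-aware comparison should be added

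*SAP*

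**What the plan says.** The SAP's Safety objectives section makes the safety question comparative: "The safety objective is to compare the safety and tolerability of Vx-001 treated" against placebo-treated patients.

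Under Safety endpoints, Adverse events, reporting starts at signature of consent and continues "up until 4 weeks after the end of the treatment visits". Treatment has no fixed length. Under Study design and randomisation, the six initial injections are "followed by vaccinations with 2mg ARG-Vx001 every 12 weeks commencing at week 27 until disease progression", unless the patient withdraws for another reason.

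Section 5.2.5.1 (Adverse events tabulations) counts how many patients had each event at least once and gives the percentage. For the six rows of Table 32 it adds: "95% confidence intervals will be calculated for the incidence rates in each treatment group, together with a confidence interval for the treatment group difference". These so-called incidence rates are therefore proportions. For proportions, the Presentation of results section says that "confidence intervals of proportions will be calculated using the Clopper-Pearson method", a binomial method with no time term.

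Section 5.2.3 summarises the number of vaccinations and the "duration (number of days) between first IP administration and last IP administration" by arm in Table 31. None of the AE tables in Appendix 1 (Tables 32 to 40) uses patient-time, time to first event or a common observation period.

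**The concern.** A patient who stays on treatment longer is observed for AEs longer and has more opportunity to record a first event. The percentage with at least one event mixes the rate at which events arise with the length of observation. The plan treats time on treatment as something the vaccine may change: time to treatment failure, which counts early withdrawal or a new anti-tumour treatment, is a secondary comparison.

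If Vx-001 keeps patients on treatment longer, the crude difference can suggest harm that is only longer observation. If patients leave Vx-001 sooner, a real excess can be diluted. Either way, the only interval offered for the arm comparison does not separate the two explanations.

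**Working it through.** **Inputs from the SAP.** 110 patients per arm; 12-month survival of 43% on placebo and 58% on Vx-001 (revised sample-size section); AE window ending 4 weeks, or 0.92 months, after treatment.

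**Inputs the SAP does not give, so assumed.** Exponential time on treatment with a placebo median of 3 to 6 months; the same constant AE hazard λ in both arms, 0.02 to 0.10 per month; and a hazard ratio (HR) for stopping treatment, Vx-001 against placebo, of 0.8 or 0.645.

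**Plan's own figures.** The safety section states none. The value 0.645 is the planned survival effect: ln 0.58 / ln 0.43 = 0.645. The same exponential assumption gives medians of 12 × ln 2 / 0.844 = 9.9 and 12 × ln 2 / 0.545 = 15.3 months, close to the stated 9.8 and 15.2. Applying this ratio to treatment duration is borrowing, not something the SAP says.

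**Formula.** With treatment-stopping rate μ, counting from first injection:

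P(at least one event) = 1 − exp(−0.92 λ) × μ / (μ + λ)

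**Central case.** Placebo median 4 months, so μ = ln 2 / 4 = 0.1733; λ = 0.05.

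- Placebo: 1 − 0.9550 × 0.1733 / 0.2233 = 25.9%.
- Vx-001 at HR 0.645, μ = 0.1118: 1 − 0.9550 × 0.1118 / 0.1618 = 34.0%, a difference of 8.1 points.
- Vx-001 at HR 0.8: 29.8%, a difference of 3.9 points.
- Half-width of the 95% CI for the difference: 1.96 × √[(0.259 × 0.741 + 0.340 × 0.660) / 110] = 12.1 points.

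**Range.**

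| λ per month | Placebo median (months) | Placebo | Vx-001, HR 0.8 | Vx-001, HR 0.645 |
| --- | --- | --- | --- | --- |
| 0.02 | 3 | 9.6% | 11.4% (+1.8) | 13.4% (+3.8) |
| 0.02 | 6 | 16.3% | 19.3% (+3.0) | 22.6% (+6.3) |
| 0.05 | 4 | 25.9% | 29.8% (+3.9) | 34.0% (+8.1) |
| 0.10 | 3 | 36.3% | 40.8% (+4.5) | 45.4% (+9.1) |
| 0.10 | 6 | 51.1% | 56.2% (+5.1) | 61.1% (+9.9) |

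**How often the interval misleads.** Using the normal approximation for the difference, with placebo medians of 3 to 6 months and placebo incidence from 10% to 95%, the 95% CI excludes zero in 5% of trials when durations are equal. This becomes 6 to 12% when Vx-001 duration is 1.25 times longer (1/0.8), and 9 to 32% when it is 1.55 times longer (1/0.645).

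**Where it shrinks.** At 95% placebo incidence the difference is only +0.9 points (1.25 times) or +1.6 points (1.55 times). For early-clustering events, take λ = 0.05 to week 18 (4.14 months), a quarter of that afterwards, and a placebo median of 4 months. The crude percentages are then 18.6% against 22.2% at HR 0.645 (+3.6), or 20.3% at HR 0.8 (+1.7).

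**Check on the possible remedies.** In that same early-loaded case, with identical hazards in both arms, first events per patient-month are 0.0332 on placebo and 0.0282 on Vx-001 at HR 0.645, a spurious rate ratio of 0.85; at HR 0.8 it is 0.92. Under a constant hazard the ratio is 1.00. A crude table cut at week 18 is not clean either. The share of AE windows closed by then is 1 − exp(−μ × (4.14 − 0.92)), which is 43% on placebo and 30% on Vx-001 at HR 0.645.

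**The case against.** The best defence is that crude AE percentages are the usual description, that nothing is decided on them, and that the reader has Table 31 and listings with time since vaccination. Section 5.3.5 reserves definitive efficacy conclusions for the primary analysis, and Table 32 carries no test or decision rule. This stands in part: the matter is one of misreading safety, not of type I error. But Table 31 lets a reader suspect unequal observation without correcting for it, and the stated objective is to compare arms.

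A reader might infer that the longer-treated arm must show more AEs by construction. The SAP does not support that. It states neither that durations will differ nor that events keep arising at a steady rate. Injections go from every 3 weeks to every 12 weeks, so injection-related events may well cluster early, where the gap is small. Rows such as any AE may be nearly saturated. Collection also begins at consent, so the any-AE and any-SAE rows include pre-treatment events that treatment duration cannot affect. Visits thin out late ("visits every 3 weeks from randomization to week 15 and every 12 weeks from week 27 until the end of study treatment"), but equally in both arms, so this creates no arm difference by itself.

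It is also fair that exposure-adjusted rates should not simply replace the crude comparison: with early-loaded events they can make the longer-treated arm look safer than it is.

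**Conclusion.** The point holds conditionally. Given a window tied to treatment duration and a comparison of crude percentages, any difference between arms in time on treatment biases the treatment-emergent rows of Table 32, in expectation, towards more events in the arm treated longer. Under the stated assumptions the size is 1.8 to 5.1 points at a duration HR of 0.8 and 3.8 to 9.9 points at 0.645, against a CI half-width of about 12 points in the central case. That is enough to shift how the interval reads, but usually not enough to push it clear of zero.

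The size rests on assumed durations, assumed constant and equal AE hazards, and a survival HR borrowed for treatment duration. It falls to about 1 to 2 points for near-universal events and to about 2 to 4 points in the early-loaded example. A reader might also infer that Vx-001 will look worse; the direction is not known, because the SAP makes no assumption about time to treatment failure. The primary analysis is unaffected. This is an inexpensive improvement worth making before lock and unblinding.

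**What to change.** In section 5.2.5.1:

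- Keep Table 32 with its crude percentages and intervals, and state that the crude difference is to be read together with exposure in Table 31.
- For the treatment-emergent rows, add time from first injection to first event. Report cumulative incidence with 95% CIs for each arm and for the arm difference at week 18. Patients leave observation at the end of their own AE window, and death is treated as a competing event.
- Give exposure-adjusted incidence rates (patients with a first event divided by patient-time to first event or end of window) as a supplement, not as the sole basis for comparing arms.

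The cost is SAP wording and one extra table; event onset and injection dates are already collected. There are two limits. Exposure-adjusted rates assume a roughly constant hazard and can mislead when events cluster around the early 3-weekly injections. The cumulative incidence estimate assumes that leaving observation is unrelated to AE risk, so it reduces the bias rather than guaranteeing its removal.
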